#### Feasibility of the intervention (process evaluation)

Nine months after the training, a follow-up session will be organised for the dental therapists who are participating in the intervention group. During this session, semi-structured focus group interviews will be conducted to explore dental therapists’ perceptions about the feasibility of the intervention. The focus group interview will cover the following topics: experiences and challenges with the use of the interview method, perceived usefulness of the supporting materials (script and cards), their impressions regarding parents’ acceptance and appreciation of the approach, and suggestions for improvement of the intervention. Prior to the focus group interview, dental therapists are requested to complete a questionnaire on the same topics to supplement the qualitative data. The interview guide and questionnaire are presented in Additional files 3 and 4, respectively.

In addition, individual telephone interviews will be conducted with a random selection of 20 parents who received the intervention. Parents will be asked about their perceptions of the interview, and about whether or how it helped them to improve parenting strategies to facilitate tooth brushing for their children. The focus group and telephone interviews will be audio-recorded and transcribed verbatim.

#### Measures of fidelity

Fidelity is defined as the extent to which delivery of an intervention adheres to the protocol originally developed [38]. To measure fidelity, dental therapists in the intervention group will be requested to document the selected barriers and action points of participants. Questions on the implementation of the intervention are included in the questionnaire and focus group interview with dental therapists (see Additional files 2 and 3). In addition, the 20 parents who will be contacted for a telephone interview will be asked to give a description of their research visit, to determine whether the study protocol was followed as intended.

To assess whether the target group is reached, dental therapists in both intervention and control practices will be requested to document the number of subjects that agreed to participate out of the number of eligible subjects that were approached, as well as reasons not to participate. Non-participating parents will be asked two questions on their highest completed level of education and country of birth, to be able to assess potential selection bias.

#### Timeline

The timeline of the study, including the overview of research visits and data collection, is shown in Fig. 2.

**Fig. 2 Fig2:**
[figure not shown]
Timeline of the study

### Statistical analysis

All data will be coded with a unique ID, and data will be securely stored at the Department of Social Dentistry at ACTA. The analysis will be performed in STATA. Differences in the primary outcome (dmfs and the combined ICDAS scores ‘B and C’ and ‘A, B and C’) between children in the intervention and control group at T2 will be analysed using zero-inflated Poisson or negative binomial regression. Baseline differences in children’s dmft scores (obtained from dental records) will be taken into account.

Differences in the three tooth brushing-related outcomes between children in the intervention and control group at T1 and T2 will be analysed using ordered logistic or logistic regression (for tooth brushing frequency in children; either treated as a ordinal variable or dichotomous variable, depending on the distribution of responses), and linear or negative binomial regression (for parental self-efficacy scores and children’s plaque scores).

All analysis will be adjusted for clustering of observations within dental practices. In case of significant differences in co-variates (moderators) between the intervention and control group at baseline (T0), the analysis will be adjusted accordingly for these co-variates, or in case of sufficient power, a sub-group analysis will be performed. An intention-to-treat analysis will be conducted to account for participants that will be lost to follow-up. Statistical significance is set at α = 5%.

Qualitative data from the focus group interviews and telephone interviews will be processed using the Maximised Qualitative Data Analysis programme (Verbi-software MAXQDA). Conventional content analysis will be used to identify emergent themes and concepts related to the feasibility and acceptability of the intervention.

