### The intervention

All children, in both the intervention and control group, will receive care as usual, consisting of regular dental check-ups, dental health education following the Ivory Cross national guideline, and if indicated, preventive treatment (fluoride varnish and/or fissure sealants) and/or caries treatment (fillings, non-restorative caries treatment or extractions) [27]. Regular dental check-ups for young children are generally scheduled every 6 months, or at shorter intervals when children are identified as having an increased caries risk. Key oral health messages of the Ivory Cross national guideline include twice daily tooth brushing with fluoride toothpaste (500–750 ppm fluoride), reducing the frequency of carbohydrate intakes to three main meals and a maximum of four (healthy) snacks per day, and avoiding foods and drinks before or during bed time [4]. In addition to care as usual, parents of children in the intervention group will receive supplementary support to adhere to the advice of twice daily tooth brushing with fluoride toothpaste, following the ‘Uitblinkers’ intervention.

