### Outcome measures

The primary outcome of this trial, children’s dental caries experience after 24 months, are measured at T2. Secondary outcomes, namely ^1)^ parents’ self-efficacy (confidence) in brushing their children’s teeth when experiencing barriers, ^2)^ tooth brushing frequency in children, and ^3)^ children’s dental plaque scores, are measured at T0.0, T1 and T2. The intervention is considered successful when a 25% reduction in dental caries experience is observed in the intervention group in comparison to the control group, which equals a reduction of 1.5 to 2.0 dmfs. Tooth brushing-related outcomes are assessed to provide additional information on the intervention’s effect and on the pathways by which the intervention might affect children’s caries experience. If one of more tooth brushing-related outcomes are significantly more favourable in the intervention group compared to the control group, but dental caries experience is not reduced by at least 25%, the intervention is not considered successful.

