#### Clinical outcome: children’s dental caries experience

At T2, a clinical oral examination will be performed to assess children’s dental caries experience. The clinical oral examination will only include a visual inspection and no x-rays will be taken. Dental caries status will be assessed using the merged International Caries Detection and Assessment System (ICDAS) coding system [35], which classifies dental caries into sound (‘0’), initial stage of decay (‘A’), moderate decay (‘B’) or extensive decay (‘C’). In addition, the dmfs-index will be scored according to WHO Basic Methods for Oral Health Surveys [36]. The oral examinations will be performed by one dentist from each control or intervention practice, after they have received training from a certified ICDAS trainer for calibration and standardisation purposes. The training will be organised 23 months after inclusion of the first participants. During the training, the dentists’ intra- and inter-examiner reliability will be assessed; a minimum weighted kappa of 0.60 for both the intra and inter-examiner reliability is required to certify as an examiner [37]. In case of lower reliability scores, more training will be provided. The dmft and dmfs at baseline will be extracted from personal dental health records from the dental practice, in order to compare differences in dental caries experience between intervention and control children at baseline, and to adjust for potential differences in the analysis.

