## Abbreviations

ASA: American Society of Anaesthesiologists
dmfs: Decayed, missing and filled surfaces
dmft: Decayed, missing and filled teeth
ICDAS: International Caries Detection and Assessment System
OHP: Oral healthcare professional
WHO: World Health Organization

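### Two of the three primary caries measures, the combined ICDAS scores, count only decay present at T2 as described, so surfaces filled or extracted during follow-up are lost from a measure meant to capture caries experience

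*Protocol article*

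**What the plan says.** All references are to the protocol article.

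- **Outcome measures** states the construct: "The primary outcome of this trial, children’s dental caries experience after 24 months, are measured at T2".
- **Statistical analysis** gives three measures of it: "Differences in the primary outcome (dmfs and the combined ICDAS scores", the latter formed once from codes B and C and once from codes A, B and C. All three stand inside the primary outcome, and none is ranked above the others.
- **Clinical outcome: children's dental caries experience** introduces the coding: "Dental caries status will be assessed using the merged International Caries Detection and Assessment System (ICDAS) coding system". It says that this system "classifies dental caries into sound (‘0’), initial stage of decay (‘A’), moderate decay (‘B’) or extensive decay (‘C". No code for a filled or missing surface is described. The section then continues: "In addition, the dmfs-index will be scored according to WHO Basic Methods for Oral Health Surveys".
- **Abbreviations** defines the second index: "dmfs: Decayed, missing and filled surfaces".
- **The intervention** says that care as usual, given in both groups, includes, if indicated, "caries treatment (fillings, non-restorative caries treatment or extractions").
- **Co-variates** says that restorative and preventive treatments received during the study will be taken from dental records so that the analysis can adjust for them. The primary-analysis text names baseline dmft, clustering, and covariates that differ at baseline. It does not name treatment during follow-up.
- **Power calculation** and **Outcome measures** express the detectable difference and the success threshold in dmfs only.

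**The concern.** Caries experience is cumulative: a lesion that has been filled, or has led to an extraction, still belongs to it. The dmfs respects this through its missing and filled components. A sum of ICDAS decay codes, as the article describes them, does not. It records the decay still present on the day of the T2 examination.

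Measures named together as one primary outcome can therefore disagree about the same disease. A child with four affected surfaces, all filled before T2, scores 0 on the B and C sum and 4 on dmfs. A child with one unfilled moderate lesion scores 1 on each.

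Between groups, the risk is that a difference in how much decay has been filled or extracted by T2 appears as a difference in caries, or hides one. Practices are not randomised. Intervention practices volunteer, and matching covers practice size and regional socioeconomic status, not treatment policy. The article has no rule for the case in which the ICDAS scores and dmfs point in different directions.

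**Working it through.** **Plan's own figure.** The article gives no expected value for the ICDAS scores, so none can be reproduced. The related figure is the success threshold: 25% of the mean dmfs of 6.9 in the Power calculation is 0.25 × 6.9 = 1.725, which lies inside the stated range of 1.5 to 2.0 dmfs. The threshold is thus a dmfs quantity.

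**What each measure retains**

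| Status of an affected surface at T2 | ICDAS sums as described | dmfs |
|---|---|---|
| Decay present, at a stage the measure includes | counted | counted as d |
| Filled | not counted | counted as f |
| Extracted for caries | not counted | counted as m |

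**Effect on the group comparison.** Let pC and pI be the shares of affected surfaces filled or extracted by T2 in the control and intervention groups. Expected decay still present is experience × (1 − p), so:

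observed ratio = true ratio × (1 − pI) / (1 − pC)

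The documents give neither share. The values below are assumptions chosen to show a range.

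| True ratio | pC | pI | Calculation | Observed ratio |
|---|---|---|---|---|
| 1.00 | 20% | 20% | 0.80 / 0.80 | 1.00 |
| 1.00 | 30% | 40% | 0.60 / 0.70 | 0.857 |
| 1.00 | 20% | 30% | 0.70 / 0.80 | 0.875 |
| 1.00 | 20% | 40% | 0.60 / 0.80 | 0.75 |
| 1.00 | 40% | 20% | 0.80 / 0.60 | 1.33 |
| 0.75 | 30% | 30% | 0.75 × 0.70 / 0.70 | 0.75 |
| 0.75 | 40% | 20% | 0.75 × 0.80 / 0.60 | 1.00 |

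Equal shares preserve the true ratio. A 10-point gap moves a null ratio to about 0.86 to 0.88. A 20-point gap can produce an apparent 25% reduction or cancel a real one. In every row the dmfs ratio equals the true ratio, provided that each treated surface is scored m or f.

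**Do the planned adjustments repair this?**

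- *Baseline dmft.* This includes filled and missing teeth, whereas the ICDAS sums as described exclude them. Children with dmft up to 3 can enter, because exclusion starts at 4. A child with three teeth filled before baseline has a raised covariate, but those teeth add nothing to the outcome unless they decay again.
- *Treatment from dental records.* Treatment happens after baseline and results from caries. Adjusting for it conditions on a consequence of the outcome, and the primary-analysis text does not include it.

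**The case against.** The strongest reply is that the article never says that filled and missing surfaces are left out. It summarises a published coding system in one sentence and calls the outcome caries experience. The combined scores could be cut-offs for the decayed component, to be used with m and f. An article may leave such a derivation to a fuller document. That reading is possible, but it is not what the text says: the only things described as combined are the letter codes, and dmfs is introduced as an additional index. If m and f are intended, one sentence settles the point.

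Three further objections stand in part.

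- The article plans to collect treatment data for adjustment, so the authors saw that treatment could matter. This is fair, although the remedy is insufficient for the reasons shown above.
- Evidence that treated shares will differ is thin. The Discussion concedes possibly higher motivation for preventive care in intervention practices, not more fillings. Both groups are told to follow the same guidelines. This limits what can be said about the likely size and direction of any bias.
- Care as usual also includes non-restorative caries treatment, which places no filling. The share p must therefore be read as filled or extracted, not as all treatment.

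A reader might infer that the ICDAS scores measure how much a practice treats and not disease, or that a spurious 25% fall in them would satisfy the trial's success criterion. The documents support neither inference. The scores reflect both disease and treatment, and the criterion is expressed in dmfs, which keeps filled and missing surfaces.

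**Conclusion.** The point holds in a limited form. As described, two of the three named primary measures count decay present at T2 and omit surfaces filled or extracted, so they do not match the stated construct.

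The mismatch follows from the text. Bias between groups does not follow automatically: it requires unequal shares filled or extracted. Under assumed shares, gaps of 10 to 20 points shift a null ratio from 1.00 to between 0.875 and 0.714 when the intervention group has the higher share (20% against 30% at one end; 30% against 50%, that is 0.50 / 0.70, at the other). The shift is upward when the gap is reversed. With equal shares it is zero.

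The dmfs comparison, the sample size and the success threshold are not affected if treated surfaces are scored as m or f. What is exposed is the interpretation of the two ICDAS comparisons, which have equal primary standing and no rule for disagreement with dmfs.

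**What to change.** Define the two ICDAS-based measures as caries experience, with each surface counted once:

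- (B + C) + m + f surfaces
- (A + B + C) + m + f surfaces

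Take m and f from the dmfs scored at the same T2 examination. Report the plain B + C and A + B + C counts descriptively, labelled as untreated decay.

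Alternatively, make dmfs the sole primary measure, in line with the sample size and the success threshold, and move the ICDAS counts to secondary outcomes.

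Either option costs a sentence of definition and, for the first, a derived variable. No extra examination or data collection is needed. The choice should be recorded before T2 data are analysed.

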## Methods

### Design and study setting

The study is designed as a non-randomised cluster-controlled trial with a duration of 24 months. The study will be conducted in general dental practices located in The Netherlands. The medical ethical committee of the Vrije Universiteit in the Netherlands has provided ethical approval for this study (no. 17397).

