#### Children and their parent(s)

Each dental practice, both in the intervention and control group, will recruit a sample of at least ten 3 to 4-year-old children from their own patient population for inclusion in the study, using a simple random sampling method. Eligible children will be listed from the patient registry and given a random number by the coordinating dental therapist, using the website http://random.org. Subjects will be approached in numerical order until at least ten subjects are included. In cases of twins, only one child of the family will be selected. Children will be eligible to participate if they are healthy (ASA classification I) and between 36 and 59 months old at the time of inclusion. Exclusion criteria are:
Children with a physical or mental disability,Children with a high caries activity (decayed, missing and filled teeth (dmft) ≥ 4), based on the patient dental record,Children with hypomineralised second primary molars,Children (or siblings of the child) who have been receiving treatment at a referral practice for paediatric dental care,Children of parents who do not speak and understand the Dutch language.

Three to 4-year-olds are selected for two reasons. First, the restriction of the age group reduces variation in dental caries levels, allowing better comparison of the intervention’s effect. Second, children are preferably targeted from a young age when oral health behaviours are still shaped and more amendable to change. However, in The Netherlands only 35% of two-year-olds are visiting the dentist, which increases to 95% when children reach the age of four [25]. Therefore, the choice was made to include 3 to 4-year-old children, increasing the number of young children that can be reached. Parents will be informed about the study aim and procedures, privacy and confidentiality regulations and their rights to withdraw at any time using an information letter (Additional file 1). Prior to participation, written informed consent will be obtained from the parents by the dental therapist.

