#### Power calculation

The primary expected outcome of the study is a lower dental caries experience in the intervention group, compared to the control group, after 24 months. A power calculation indicated that a sample of 330 children will be required (165 children in each group) to detect a minimum difference of 2 decayed, missing and filled surfaces (dmfs) between the intervention and control group. This calculation is based on the following parameters: 80% power, a significance level of 5%, a mean dmfs of 6.9 ± 6.2 in 6-year-old children in the Dutch population [26], an expected loss to follow-up of 20 and 15% excess to account for clustering in the analysis. Further analyses indicated that a sample of 330 children will be amply sufficient to detect differences in tooth brushing-related outcomes.

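### For the T2 dmfs comparison the analysis section names baseline dmft, although baseline dmfs is also collected for adjustment

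*Protocol article*

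**What the plan says.** The Protocol article deals with baseline caries in three places.

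- **Statistical analysis.** The outcomes to be compared at T2 are introduced as "Differences in the primary outcome (dmfs and the combined ICDAS scores ‘B and C’ and ‘A, B and C". The one baseline caries score named for these models is dmft: "Baseline differences in children’s dmft scores (obtained from dental records) will be taken into account".
- **Clinical outcome: children's dental caries experience.** Both indices are collected: "The dmft and dmfs at baseline will be extracted from personal dental health records from the dental practice". The same sentence gives the purpose, which is to compare the groups at baseline "and to adjust for potential differences in the analysis".
- **Children and their parent(s).** An exclusion criterion reads "Children with a high caries activity (decayed, missing and filled teeth (dmft) ≥ 4), based on the patient dental record", so enrolled children have a recorded dmft of 0, 1, 2 or 3.

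The setting is given under Design and study setting: "The study is designed as a non-randomised cluster-controlled trial with a duration of 24 months". Other covariates enter only conditionally: "In case of significant differences in co-variates (moderators) between the intervention and control group at baseline (T0". The Co-variates section lists sociodemographic items, other oral health behaviours and treatments received during the study. It does not list baseline dmfs.

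**The concern.** dmfs is cumulative, so surfaces already decayed, missing or filled at T0 are part of the T2 count. The natural baseline covariate is the same index at T0. dmft is related to it but coarser: two children with the same number of affected teeth can have quite different numbers of affected surfaces, and a model with dmft alone treats them as equal at baseline.

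With random allocation this would mainly cost precision. Here intervention practices volunteer, and controls are matched only on practice size and regional socioeconomic status. Usual care allows a decayed tooth to be filled, managed without restoration or extracted. Surfaces per affected tooth could therefore differ by practice, and practice is the unit of allocation. Any such difference would pass through dmft adjustment into the T2 contrast. It could look like benefit or hide it, depending on its direction. Success is judged on the size of the dmfs reduction, so a few tenths of a surface could matter.

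**Working it through.** **Reference figure.** Outcome measures defines success as a 25% reduction, equated with 1.5 to 2.0 dmfs. Power calculation gives a mean dmfs of 6.9 and an SD of 6.2. Then 0.25 × 6.9 = 1.725, which lies inside the stated range. The trial is sized "to detect a minimum difference of 2 decayed, missing and filled surfaces (dmfs". No stated figure is disputed on this point.

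**What dmft adjustment can and cannot remove.** Let T be mean baseline dmft in an arm, m mean surfaces per affected tooth, and b the number of T2 surfaces per baseline surface. Mean baseline dmfs is T × m. The T2 difference due to baseline alone is b × (T_I m_I − T_C m_C), for intervention (I) minus control (C). If m is equal in the arms, this is b × m × (T_I − T_C), which dmft captures. If T is equal, it is b × T × (m_I − m_C), which dmft cannot see.

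**Assumed inputs.** The documents give no baseline dmft or dmfs distribution, so all of the following are assumptions:
- dmft of 0 to 3, with 55 to 70% of children at 0
- 1 to 5 surfaces per affected tooth, with means of 2 to 3
- b from 1 to 2
- no intervention effect
- linear regression with 200,000 simulated children per arm

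The table shows the spurious T2 difference in dmfs, intervention minus control.

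| Assumed imbalance (control v intervention) | Unadjusted | Adjusted for dmft | Adjusted for dmfs |
|---|---|---|---|
| Teeth only: T 0.84 v 0.52, m 2.0 in both | −0.6 to −1.3 | about 0 | about 0 |
| Surfaces per tooth only: T 0.73 in both, m 2.25 to 3.0 v 2.0 | −0.2 to −1.5 | −0.2 to −1.5 | within 0.05 of 0 |
| Both: T 0.84 v 0.52, m 2.5 v 2.0 | −1.1 to −2.2 | −0.3 to −0.7 | within 0.05 of 0 |

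**Hand checks (absolute values).**
- Row 1: (0.84 − 0.52) × 2.0 = 0.64 at b = 1 and 1.28 at b = 2.
- Row 2: 0.73 × 0.25 × 1 = 0.18 at the low end and 0.73 × 1.0 × 2 = 1.46 at the high end.
- Row 3: 0.84 × 2.5 − 0.52 × 2.0 = 1.06 at b = 1 and 2.12 at b = 2. At b = 1 the simulated difference falls from 1.076 to 0.325 after dmft adjustment, so 1 − 0.325/1.076 = 70% is removed.

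The correlation of baseline dmft with dmfs was 0.93 to 0.94 in these runs, and 0.88 to 0.91 under another assumed set of surface distributions.

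**Precision.** Under that other set, the SD of baseline dmfs left unexplained by dmft is about 1.2. At b = 1 this is (1.2/6.2)² = 4% of outcome variance, a small gain. At b = 2 the same arithmetic gives (2.4/6.2)² = 15%. The case for the change rests on bias rather than precision.

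**The case against.** **The clinical outcome section already commits to adjustment.** Its sentence on baseline extraction covers both indices and gives adjustment as a purpose. A reader might infer from the analysis section that the sponsor decided to leave dmfs out, but the documents do not support that. They show two sections that disagree, and the analysis section may simply be loosely worded. It is still the section an analyst would follow, and it names the tooth count.

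**dmft does most of the work.** A reader might also infer that baseline surface differences in general stay in the result. They do not. dmft adjustment removes all of an imbalance in the number of affected teeth and about 70% of the mixed imbalance above. Only a systematic difference in surfaces per affected tooth survives in full, and no section reports one. This stands, and it is why the range starts at zero.

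**The 0 to 3 range is not a source of bias.** It is tempting to say that the entry criterion distorts the adjustment. It makes dmft coarse, but it also limits how far the arms can differ at baseline, in surfaces as well as teeth.

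**Any single percentage is fragile.** With 2.1 v 1.6 surfaces per tooth and mean dmft 1.0, the leftover is 0.5 dmfs, or 0.5/1.725 = 29% of the success threshold. With mean dmft 0.74 it is 0.37 dmfs, or 21%. Neither input is in the documents. The arithmetic is also additive, whereas zero-inflated Poisson or negative binomial models are planned.

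**Recorded surface counts may be unreliable.** Examiner training comes 23 months after first inclusion and serves the T2 examination, so baseline values are uncalibrated. This is a fair reason to keep dmft for a sensitivity analysis. It does not favour dmft outright, because dmft comes from the same records.

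**Conclusion.** The point holds as an inconsistency with a practical consequence. The analysis section names only baseline dmft for a surface-count outcome, while the clinical outcome section collects dmft and dmfs for adjustment. Followed literally, the analysis section uses the less suitable baseline in a non-randomised comparison and leaves any between-arm difference in surfaces per affected tooth in the T2 dmfs contrast.

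The size cannot be derived from the documents. Under the stated assumptions the leftover is about 0 to 1.5 dmfs, against a success threshold of 1.5 to 2.0 dmfs. This is a range of possibilities from a linear illustration, not an estimate for this trial. Adjusting for dmfs brought the spurious difference to within 0.05 of zero in every scenario, but those scenarios assume that baseline surfaces are recorded without error. The calculation covers the dmfs outcome only, not the combined ICDAS scores.

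**What to change.** In Statistical analysis, name baseline dmfs from the dental records as a prespecified covariate in the primary T2 dmfs model, included whether or not the arms differ significantly at baseline. This brings the section into line with the clinical outcome section. The functional form can be left to the analysis plan, and dmft can be kept as an optional sensitivity adjustment.

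The cost is one sentence, settled before T2 data are seen. No new data are needed and no stated figure changes. The small downside is reliance on surface counts from routine, uncalibrated records, which the dmft sensitivity analysis would help to judge.
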